## Abstract

**Background:**

Bullying is a major problem worldwide and Chile is no exception. Bullying is defined as a systematic aggressive behavior against a victim who cannot defend him or herself. Victims suffer social isolation and psychological maladjustment, while bullies have a higher risk for conduct problems and substance use disorders. These problems appear to last over time. The KiVa antibullying program has been evaluated in Finland and other European countries, showing preventive effects on victimization and self-reported bullying. The aims of this study are (1) to develop a culturally appropriate version of the KiVa material and (2) to test the effectiveness of the KiVa program, with and without the online game, on reducing experiences of victimization and bullying behavior among vulnerable primary schools in Santiago (Chile), using a cluster randomized controlled trial (RCT) design with three arms: (1) full KiVa program group, (2) partial KiVa (without online game) program group and (3) control group.

**Methods and design:**

This is a three-arm, single-blind, cluster randomized controlled trial (RCT) with a target enrolment of 1495 4th and 5th graders attending 13 vulnerable schools per arm. Students in the full and partial KiVa groups will receive universal actions: ten 2-h lessons delivered by trained teachers during 1 year; they will be exposed to posters encouraging them to support victims and behave constructively when witnessing bullying; and a person designated by the school authorities will be present in all school breaks and lunchtimes using a visible KiVa vest to remind everybody that they are in a KiVa school. KiVa schools also will have indicated actions, which consist of a set of discussion groups with the victims and with the bullies, with proper follow-up. Only full KiVa schools will also receive an online game which has the aim to raise awareness of the role of the group in bullying, increase empathy and promote strategies to support victimized peers. Self-reported victimization, bullying others and peer-reported bullying actions, psychological and academic functioning, and sense of school membership will be measured at baseline and 12 months after randomization.

**Discussion:**

This is the first cluster RCT of the KiVa antibullying program in Latin America.

**Trial registration:**

ClinicalTrials.gov, Identifier: NCT02898324. Registered on 8 September 2016.

**Electronic supplementary material:**

The online version of this article (doi:10.1186/s13063-017-1810-1) contains supplementary material, which is available to authorized users.

## Background

All children and youth should be offered a safe learning environment where they are treated equally and with respect. Research on school bullying has shown that despite many efforts, this ideal is far from reality for many school-aged children. Bullying, defined as repeated aggressive or harmful actions directed at a less powerful peer [1, 2], is highly prevalent in schools worldwide. In a large study involving 40 countries, 10.7% of students reported bullying others on a regular basis, 12.6% said that they were repeatedly bullied by their peers, and 3.6% reported being both perpetrators and victims of bullying [3]. Large-scale surveys conducted in Chile, although scarce, have indicated similar or even higher prevalence of the problem [4, 5].

Bullying compromises equal learning opportunities, safety and wellbeing of millions of children and youth around the world. Research shows that the quality of peer relations, especially emotional support (or lack of it) from peers, has significant consequences for school motivation, engagement and achievement [6]. Apart from reducing targeted students’ liking of (and presence at) school, as well as their motivation and achievement, victimization has short- and long-term psychosocial and mental health consequences, such as depression and anxiety [7, 8]. Bullying perpetration, on the other hand, is associated with later criminal offending [9]. Besides victims and perpetrators, bullying even has negative outcomes for classmates who are merely witnessing the bullying [10, 11].

The call for effective prevention of bullying has resulted in numerous school-based programs developed for this purpose. According to the meta-analysis by Ttofi and Farrington [8], such programs reduce the prevalence of bullies and victims on average by 17–23% but the effects of different programs vary substantially. Furthermore, even programs that were proven to be effective in one study, often in their country of origin, have sometimes produced little or no effects in replication studies in new contexts. More research on the generalizability of evidence-based programs across (culturally) diverse groups, countries and contexts is needed. Carrying out such research in Chile, where there is urgent need for evidence-based prevention of bullying, is highly relevant. Despite government-supported initiatives and guidelines to help schools deal with bullying (“Ley N° 20536: Sobre violencia escolar,” 2011 [12]), no randomized controlled trials (RCT) have been carried out in Chile in order to test the effectiveness of existing antibullying programs.

The KiVa antibullying program (an acronym for Kiusaamista Vastaan, “against bullying”), developed at the University of Turku, is widely used in Finnish schools. KiVa has been evaluated in a large RCT and during its nationwide dissemination in Finland [13–15], with positive effects being shown on numerous variables, including bullying and victimization, depression, anxiety, enjoyment of school and academic motivation. There are also experiences in other parts of Europe showing good results [16, 17]. The KiVa program involves indicated actions (targeted at students who have been involved in bullying as perpetrators or victims): they refer to a series of discussions with the bullies and their victims with a proper follow-up procedure. The universal actions (targeted at all students as potential witnesses of bullying) on the other hand, consist of ten 2-h student lessons delivered during a school year, with the aim to raise awareness of the role of the peer group in bullying, increase empathy towards bullied students, and promote bystander strategies to support and defend their victimized peers. The universal actions also include posters, highly visible vests for recess supervisors and, finally, an innovative digital learning environment, an antibullying computer game [18] that can be played with PC or tablet computers, either during (there are special slots deserved for this in the curriculum) or between lessons.

The digital KiVa game involves five levels, the topics of which match the contents of the 10 student lessons. Each level includes three modules: “I Know,” “I Can,” and “I Do.” In the I Know module, the students learn new facts about bullying, but also test what they have learnt during the lessons so far. They are asked questions about the contents of the lessons in game-like quizzes, and they can test themselves with respect to different characteristics of bullying situations (e.g., Can I resist group pressure? What are my best ways to support a victimized peer?). In I Can module, the students practice the skills that they have learnt during the student lessons. They move around in a virtual school and face challenging situations in the playground, lunchroom and school corridors. They make decisions regarding how to respond to these situations, and get feedback based on their choices. In certain points of the narration the player has an opportunity to “read the minds” of the other characters (i.e., the victim or the bystanders), seeing how they think and feel. Based on these cues, and on how the episode proceeds, the player can also change their behavior and try out something different. The third module, I Do, is designed to encourage the students to make use of their acquired knowledge and skills in real-life situations. This happens by asking them to report – at each level of the game – which ones of the KiVa rules (that were adopted during the lessons) they have put into practice; for instance, whether they have treated others with respect, whether they have resisted negative group pressure, or whether they have supported someone who has been bullied. Finally, they get feedback of their performance.

A challenge of KiVa, as well as other multicomponent prevention/intervention programs, is that the relative effectiveness of the different components is unknown. Such knowledge is much needed to inform further development of the programs and to adapt them into new contexts. The implementation of the digital game as part of the KiVa program, for instance, should be justified by sound evidence showing that stronger effects can be obtained when the online game is implemented together with the other components of the program. From the public health perspective, it is necessary to assess interventions regarding their cost-effectiveness in order to provide to the community an effective intervention with the lowest cost.

In this study, investigators from Chile and Finland will collaborate on adapting the KiVa antibullying program for schools in Chile and evaluating its effectiveness in this new context. We will further investigate whether the digital game included in the KiVa program adds to the effects obtained when the program is implemented without this component. Besides its huge practical significance, the project will contribute to the scientific discussion on the replicability of antibullying interventions in new contexts, and on the possibilities of new Information and Communication Technologies (ICT) tools to reduce bullying.

## Methods and design

This is a three-arm, single-blinded (blinded only to the outcome evaluator), cluster RCT, which will compare the effectiveness of the KiVa antibullying program with the digital game component (full KiVa schools) versus the KiVa program without the digital game component (partial KiVa schools) versus usual management for bullying (control schools) in low-income schools in Santiago, Chile. Methods are in accordance with the Standard Protocol Items: Recommendations for Interventional Trials (SPIRIT) Statement (Additional file 1).

### Aims and hypothesis

#### General aim

To develop a culturally appropriate version of the KiVa antibullying program (specifically, unit 2 which is targeted at 10–12-year-old children) and to carry out a cluster RCT to test its effectiveness with and without the digital game component versus usual management for bullying in students attending years 5 and 6 in low-income schools in Santiago, Chile. The project involves two stages: first, formative work, where the research teams translate, review and adapt the KiVa program to Chile; and second, the cluster RCT.

#### Specific aims: formative work

To translate and adapt all the material (unit 2 of the KiVa program and the evaluation tools): the translation will be done by professional translators and reviewed by young researchers, supervised by the principal investigators (PI) and coinvestigators. Necessary adaptations – mainly to the surface structure of the program – will be done during the processTo validate and measure the psychometric properties of the Revised Olweus Bully/Victim Questionnaire (OBVQ): a cross-sectional study will be carried out to assess the validity and reliability of the questionnaire in a sample of students of the same age and background as the participants in the RCT. Along with the revised OBVQ, the students will answer a questionnaire that has been used to assess bullying in Chile, the Survey of Maltreatment and Abuse of Power among Students (MIAP) [19], in order to test concurrent validity

#### Specific aims: cluster randomized controlled trial

To compare the level of self-reported victimization of 5th and 6th graders attending full KiVa, partial KiVa and control in low-income schoolsTo compare the level of self-reported bullying actions of 5th and 6th graders attending full KiVa, partial KiVa and control in low-income schoolsTo compare the level of peer-reported victimization of 5th and 6th graders attending full KiVa, partial KiVa and control in low-income schoolsTo compare the level of peer-reported bullying actions of 5th and 6th graders attending full KiVa, partial KiVa and control in low-income schoolsTo compare the level of self-reported psychological difficulties of 5th and 6th graders attending full KiVa, partial KiVa and control in low-income schoolsTo compare the level of self-reported psychological strengths of 5th and 6th graders attending full KiVa, partial KiVa and control in low-income schools

### Hypothesis

We hypothesize that at the end of the intervention there will be fewer students identified as targets and perpetrators of bullying in schools receiving the KiVa intervention than in control schools. Furthermore, we expect that the program effects will be stronger when the online game is implemented together with the other program components. The latter hypothesis is based on the emerging scientific literature on the usefulness of ICT tools in interventions for children and youth [20]. Finally, we hypothesize that the psychosocial adjustment of students will increase more in schools where bullying problems decrease the most.

### Setting and population

The Chilean educational system is structured into three types of primary and secondary schools: municipal state-funded schools (40.38%), subsidized schools (administered by private organizations but also receiving state funds, 52.13%) and private schools (administered by private organizations, not receiving state funds, 7.50%). The quality of the education received by students in municipal state-funded schools, based on standardized tests such as PISA [21], is lower than in private and subsidized schools. There are also more bullying problems in state-funded schools, as compared with the other types of schools (17.2% in state schools, 13% in subsidized schools, 10% in private schools) [5]. Our target sample will be these most vulnerable schools in Santiago, with students mainly coming from low- to middle-income families.

### Inclusion criteria

Our sample frame comprised all schools having primary education (year 1 to year 8), mixed-sex, located in Santiago, with two or three classes per year level and having a vulnerability index (School Vulnerability Index – National System of Equality Allocation (IVE-SINAE)) ≥75%. The IVE-SINAE is built taking into account several students’ and parental variables: health, family income, receiving state benefits. This percentage means the proportion of students in a school who are in most need.

All eligible schools will be invited to participate.

### Recruitment/allocation of schools

Randomization will be performed once all schools are recruited and after baseline in order to obtain balance with respect to size of the schools and level of self-reported victimization. Schools will be randomly assigned to either group with a 1:1:1 allocation as per a computer-generated randomization. An independent statistician will perform the randomization and allocation concealment will be ensured informing the allocation until all students have been recruited into the trial, which takes place after all baseline measurements have been completed (see Fig. 1).

**Fig. 1 Fig1:**
[figure not shown]
Flowchart

### Recruitment of students and consent process

After the school authorities accept to participate in the study, students and their parents will be informed of the study. Parents will be informed that the KiVa program will be part of the school curriculum following approval by the school and educational authorities. Also, the team will send an Informed Consent Form to parents to provide an opportunity to request the withdrawal of their children from the study assessments. Baseline information will be collected from all students, but those whose parents express their option for a withdrawal will not be subsequently assessed.

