### Control arm

The control group will receive the normal teaching activities and, if the study shows that the intervention is effective, they will receive the intervention in the following year.

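### The parent information omits the control arm, and opt-outs act only after baseline with no closing date before allocation is released

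*Protocol article*

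**What the plan says.** All references are to the protocol article.

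- **Recruitment of students and consent process.** Contact with families follows the school's agreement: "After the school authorities accept to participate in the study, students and their parents will be informed of the study". The message is: "Parents will be informed that the KiVa program will be part of the school curriculum following approval by the school and educational authorities". The form sent to parents is meant to "provide an opportunity to request the withdrawal of their children from the study assessments". The section ends: "Baseline information will be collected from all students, but those whose parents express their option for a withdrawal will not be subsequently assessed".
- **Recruitment/allocation of schools.** "Randomization will be performed once all schools are recruited and after baseline", and "Schools will be randomly assigned to either group with a 1:1:1 allocation". On concealment the printed sentence is incomplete, but its evident sense is that schools do not learn their arm before a certain point: "informing the allocation until all students have been recruited into the trial, which takes place after all baseline measurements have been completed".
- **Control arm.** What these schools get is given as: "The control group will receive the normal teaching activities and, if the study shows that the intervention is effective, they will receive the intervention in" (quote cut here; the year meant is the one after the trial year). The footnote to Table 1 repeats the condition, naming 2018.
- **Data collection.** Baseline is in November 2016. The only later assessment of all three arms that the text describes is in November 2017.
- **Data analyses.** The primary comparison is by intention to treat and adjusts for the baseline score. Sensitivity analyses for missing data are planned, with multiple imputation if needed.

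**The concern.** There are two separate problems in the consent section.

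First, the message to parents makes KiVa conditional on approval by the authorities and on nothing else. In a 1:1:1 trial it is also conditional on the draw. For a third of the schools the statement as printed does not hold in 2017.

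Second, the form offers withdrawal from the study's assessments, and the next sentence has every child complete the first of them. A refusal lodged before baseline therefore has no effect until the follow-up a year later. An opt-out settled before baseline would be a pre-randomization exclusion, which does no harm to the comparison between arms. Under the printed rule the same refusal becomes a missing outcome after randomization.

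What is at stake is loss of outcome data that could have been avoided. If forms are still accepted once schools know their arm, the loss could also differ between arms for reasons related to the arm.

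**Working it through.** **1. Figures the article gives.** The Sample size section states 39 schools, 115 children per school on average and 1495 pupils per arm.

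- Per arm: 39 / 3 = 13 schools; 13 × 115 = 1495, which reproduces the stated figure.
- Total: 39 × 115 = 4485.
- Control share: 13 / 39 = 1495 / 4485 = 33%.

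**2. Order of events.** The described sequence is: school agrees; parents informed; baseline; randomization; allocation released; intervention; November 2017 assessment. The article does not date the parent information, so its position before randomization is an inference.

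- If the message goes to all parents before randomization, it is the same in every arm, but it does not hold for the control third.
- If it goes only to parents in KiVa schools after allocation, it is accurate, but the information on which parents decide then differs by arm.

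On either reading the consent, allocation and control-arm sections need to be reconciled.

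**3. When an opt-out can act.** Baseline is taken from everyone, so an opt-out can act only on a later assessment. The one all-arm assessment left is November 2017, after allocation. Release of allocation is tied to completed recruitment and baseline, not to closure of opt-outs. Since baseline does not wait for the forms, both conditions could be met while forms are still coming in. No closing date is stated.

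**4. Pupils with a baseline and no outcome.** No opt-out rate is given, so the rates here are assumptions. Number = 4485 × rate.

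| Assumed rate | Pupils |
|---|---|
| 2% | 4485 × 0.02 ≈ 90 |
| 10% | 4485 × 0.10 ≈ 449 |
| 15% | 4485 × 0.15 ≈ 673 |

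**5. Bias if opt-out differed by arm (illustration only).** Let w be the opt-out proportion in an arm, and g the mean difference in SD between withdrawn and remaining pupils, taken as equal in both arms. The mean of the remaining pupils differs from the full mean by w × g, so the bias in the unadjusted difference has size |w₁ − w₂| × g.

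| Assumed rates | Assumed g | Bias (SD) |
|---|---|---|
| 5% v 5% | any | 0 |
| 2% v 5% | 0.25 | 0.03 × 0.25 = 0.0075 |
| 5% v 10% | 0.5 | 0.05 × 0.5 = 0.025 |
| 5% v 15% | 1.0 | 0.10 × 1.0 = 0.10 |

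**6. Scale.** The article prints its sample-size inputs only as symbols, so the ICC is assumed here, with 80% power and two-sided 5%. The design effect is 1 + 114 × ICC, and the detectable difference is (1.96 + 0.84) × √(2 / n_eff).

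- ICC 0.01: design effect 2.14; n_eff = 1495 / 2.14 ≈ 699; detectable difference about 0.15 SD.
- ICC 0.05: design effect 6.7; n_eff = 1495 / 6.7 ≈ 223; detectable difference about 0.27 SD.

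**The case against.** The strongest case on the other side has five parts.

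- **No demonstrated dependence on arm.** A message given before randomization is identical in all arms, and allocation is withheld until recruitment and baseline are complete. Opt-outs returned by then cannot depend on arm, and nothing says that forms are accepted afterwards. This stands. A reader might infer that control parents will feel let down and withdraw, so that the intention-to-treat comparison is broken. The article supports neither step.
- **The parent sentence is condensed.** Parents are first told of the study, which has a usual-management arm, and the sentence may only explain why withdrawal covers assessments and not lessons held in curriculum time. The letter itself is not shown. This stands in part: what parents actually read is unknown, but the printed summary names approval as the only condition.
- **Later withdrawal is possible in any trial.** True, and it should remain so. The avoidable part is a refusal known early that takes effect only after randomization.
- **Baseline data on lost pupils are useful.** They help compare followed with lost pupils and support the planned sensitivity analyses and imputation. This is a real cost of the change, but those methods soften the loss and do not prevent it.
- **Balancing on all pupils is valid.** A reader might infer that the school victimization level used for balance is spoiled by including children who will not be followed. It is not: a level measured before randomization on the whole year group is a legitimate balancing variable.

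**Conclusion.** The point holds as an inconsistency in the consent procedure and an open risk, not as a demonstrated bias. As printed, the message to parents does not fit a design in which 13 of 39 schools are controls. The rule that baseline is taken from all students contradicts the withdrawal offered just before it, and makes each opt-out a post-randomization loss. Because opt-outs need not close before allocation is released, withdrawal that depends on allocation is not ruled out.

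Its size cannot be computed from the article. Under the assumed rates, 90 to 670 pupils would lack an outcome. Under assumed unequal rates the bias would be 0.0075 to 0.10 SD, below the 0.15 to 0.27 SD detectable under the assumed ICCs; it is zero if rates are equal and withdrawn pupils differ from the rest to the same degree in each arm. Adjustment for the baseline score could remove part of any such bias. The change is worth making because it is cheap and prevents loss that need not occur.

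**What to change.** 1. Reconcile the consent section with the allocation and control-arm sections. Tell all parents, in the same words, that the school may be allocated to KiVa with the game, KiVa without the game, or usual teaching with KiVa the following year only if it proves effective.
2. Require opt-out forms back before the November 2016 baseline session and do not assess those children. If that cannot be arranged, close and record opt-outs before allocation is disclosed.
3. Keep the right to withdraw later. Report such withdrawals by arm and by whether they came before or after disclosure.

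The cost is a reworded letter and an earlier return date for a form already being sent. The small statistical downside is that decliners have no baseline data, so they cannot be compared with participants. No change to the balancing variable or to the primary analysis is needed.
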